**Methods/design:**

The MaDO study is a pre-post-controlled multi-centre study, that is performed in four hospitals in the Netherlands. It includes a pre and post measuring period of six months each with six months of implementation in between in at least 40 patients per hospital per measurement period.

Primary outcome measure is the percentage of patients treated in ultra short stay. Secondary endpoints are the percentage of patients treated according to protocol, degree of involvement of home care nursing, quality of care from the patient's perspective, cost-effectiveness of the ultra short stay programme and cost-effectiveness of the implementation strategy. Quality of care will be measured by the QUOTE-breast cancer instrument, cost-effectiveness of the ultra short stay programme will be measured by means of the EuroQol (administered at four time-points) and a cost book for patients. Cost-effectiveness analysis will be performed from a societal perspective. Cost-effectiveness of the implementation strategy will be measured by determination of the costs of implementation activities.

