At the uhM, an ultra short stay programme for breast cancer surgery was developed and evaluated, incorporating the aspects mentioned above. The programme consists of a structured care organisation including education and counselling, dedicated anaesthesia, active participation of the patient in her own treatment plan and in the decision to go home, and home care nursing. NABON guideline quality indicators are also incorporated in the programme (e.g. access time for the first visit to the Breast Unit, time spent in the process, number of breast conserving procedures and all diagnostic and treatment decisions being made in an appropriate multidisciplinary setting)[19]. Although the uhM programme was successful in the end, the programme was greeted with scepticism by both health care providers and members of the local breast cancer patient association. For example, in the beginning patients were discouraged by ward nurses to go home in the evening following surgery for the nurses did not trust the quality of the programme at that moment. In addition, it suffered from problems at the anaesthesiology department (e.g. administration of opioids at the recovery unit postoperatively even if patients did not suffer pain) and from organisational flaws. For instance, the day care surgery unit closed at 1800 hours and, therefore, patients operated on late in the afternoon had less recovery time as compared to those operated on early in the morning. Following on those limited opening hours, patients in need of more time to recover after 1800 hours were transferred to the inpatient ward from which discharge the same evening was rarely performed.

Traditionally, implementation strategies have been chosen for pragmatic reasons guided by personal acquaintance with a particular strategy[20]. In this project we chose to perform an extensive diagnostic analysis[20] of the problem, consisting of three issues:

1) how is current care organised?

2) how does it deviate from optimal care according to the innovative care programme?

3) what are barriers and facilitators for implementation of the ultra short stay programme?

The uhM experience accumulated valuable insight and knowledge about implementation of an ultra short stay programme for breast cancer. If such a programme is implemented on a wider scale, in other hospitals, these experiences may contribute to the design of implementation strategies that are tailored to local needs.

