### Intervention: the breast cancer care programme including ultra short stay

The intervention in this study concerns the comprehensive care programme for breast cancer surgery in ultra short stay (= ambulatory/24 hours stay setting). The key figures in the programme are the multidisciplinary team, the breast nurse, and the patient.

Traditionally, the surgeon has been the specialist who analyses the type of breast pathology presented. Preventive procedures, early diagnosis of non-palpable lesions, breast conserving therapy, and lymph node sparing therapy have raised possibilities to reduce the burden of breast (cancer) surgery. The role of the breast nurse was introduced to improve patient counselling. Through these developments, diagnosis and treatment of breast pathology have gained a more multidisciplinary character. A decrease in the burden of surgery may limit the need for hospital-based supportive care. Similarly, this leads to a demand for strict coordination of the different steps and disciplines involved. Moreover, responsibilities for aspects of care need to be reallocated to other persons: from hospital- based supportive caregiver towards informal caregiver, from clinician to nurse specialist, from in house nursing staff to outpatient nursing staff, from hospital-based nursing staff to home care nursing staff etc.

While the clinician's activities are limited to solving medical problems, the breast nurse performs all coordinating tasks to create a programme that runs smoothly.

The patient is the key figure in the process. In a one-hour consultation, following the preoperative diagnosis, the patient is informed by the breast nurse about all aspects of surgery (preparation, day of surgery, medication etc.). A checklist is used for this consultation and all oral information is supported by written information. Parts of this information (e.g. information on home care nursing and what to do in case of problems) are repeated on the morning of surgery, and at the moment of discharge.

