#### Measurements and timing of measurements (Figure 1)

**Figure 1 F1:**
[figure not shown]
**Overview patient questionnaires**. Overview of the type of questionnaires that are offered to patients and the time at which these questionnaires should be filled out.

- Information on the achievement of the targets of the implementation strategy is collected through Case Record Forms.

- Quality of care is measured from the patient's perspective through the QUOTE-breast cancer, a questionnaire that was developed by and for breast cancer patients and concerns those aspects that breast cancer patients perceive as most important when assessing quality of care[24,25]. The QUOTE-breast cancer questionnaire is filled out six weeks after surgery.

- Information on the performance of professionals is gained through Case Record Forms. The performance indicators have been developed by means of a consensus procedure in the uhM project group.

- Information on societal costs are retrieved from hospital information systems and through a prospective cost book that is filled out by patients during six weeks from the moment of discharge. The day before surgery, patients are asked to fill out a retrospective cost book to assess the patients' health-care related costs for a period of two weeks prior to surgery.

- Patients fill out EuroQol questionnaires at baseline (one day before surgery) and at 24 hours, one week and six weeks after surgery.

When patients sign informed consent and receive the questionnaires, a stamped envelope is given to them which can be used to return the set of questionnaires.

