### Statistical analyses

Intention to treat will be used for data analyses, and analyses will be performed using the SPSS package, version 12.0.1 ^® ^for Windows (SPSS INC 1989–2003). P values < 0.05 will be defined as statistically significant. The pre and post comparison of the interval scaled outcome variables will be analysed with a multivariate linear regression model. Apart from the independent variable hospital, other independent variables included in this model are type of surgery, age, informal care at home, involvement of home care nursing and starting time of surgery. Furthermore, correlation of data within a hospital are accounted for by clustered data analysis.

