### Programme cost-effectiveness

The time horizon of six weeks seems appropriate as patients may receive additional treatment after surgery (e.g. radiotherapy, chemotherapy or hormone replacement therapy). Therefore, we expect that only short-term quality-of-life effects and costs can be attributed to the ultra short stay programme. Cost analysis includes health care costs and costs outside health care such as out-of-pocket costs or productivity costs due to reduction in paid work and/or domestic activities. Health care costs refer to hospital and other health care facilities costs. Hospital costs consist of personnel, material, capacity costs, and overhead, associated with the diagnosis, surgical treatment, hospital stay and follow-up. Other healthcare costs include costs of visits to the general practitioner, medication, home care etc. Health care costs are estimated by multiplying the resource utilization with the cost price per unit. Most of these costs are estimated by using existing resource registration systems and available cost prices through the financial departments of the participating centres. If true cost prices are not available in the participating centres, 1) existing cost prices of the uhM or 2) official directive prices are used[28]. Healthcare costs incurred outside the hospital and costs outside health care are partly estimated through a structured cost book that is kept by all participating breast cancer patients during the period of six weeks following discharge. Productivity losses due to absence from work are estimated through the friction cost method[28,29]. To perform the cost-effectiveness analysis, costs and effects of patients treated according to care as usual (before implementation) will be compared to costs and effects of patients treated according to the ultra short stay programme (after implementation).

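### The pre-post model for the interval-scaled secondary outcomes adjusts for home care nursing, which the programme is designed to change, so any effect that runs through home care is left out

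*Protocol article*

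**What the plan says.** The Statistical analyses section states: "The pre and post comparison of the interval scaled outcome variables will be analysed with a multivariate linear regression model". With hospital, type of surgery and age, the independent variables named are "informal care at home, involvement of home care nursing and starting time of surgery". The same section announces intention to treat and allows for clustering within hospital.

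Elsewhere the article treats home care nursing as something the programme delivers:

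- The Background describes the programme as including "active participation of the patient in her own treatment plan and in the decision to go home, and home care nursing".
- The section on the intervention lists the tasks to be reallocated, among them "from hospital-based nursing staff to home care nursing staff".
- Table 1 has facilitation of specialised home care after surgery as a key recommendation.
- The Abstract names the "degree of involvement of home care nursing" as a secondary endpoint, and Table 2 lists it as a process indicator.
- The Programme cost-effectiveness section counts it in the cost outcome: "Other healthcare costs include costs of visits to the general practitioner, medication, home care etc".

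**The concern.** A covariate in a before-after comparison should describe differences between the two patient groups that the programme did not cause. Home care nursing is delivered after surgery, and the programme sets out to change it. Once it is in the model, the period coefficient compares patients before and after implementation as if their home care had been the same. That is a different question from whether the programme as a whole changed the outcome. It also sits badly with intention to treat, which compares the periods whatever care was received.

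Objective 2, that perceived quality of care does not deteriorate, is the most directly exposed. If home care raises or lowers patients' ratings, the adjusted coefficient can hide a deterioration or suggest one that did not occur. The cost comparison is exposed in the same way if this model is used for it.

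**Working it through.** The plan states no figure to reproduce. The check has two parts: what the article says about each questioned covariate, and what adjustment does to the estimate.

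**1. Is the covariate changed by the programme?**

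- *Home care nursing:* yes, by design. It is a component, a destination of reallocated care, a key recommendation, an endpoint and a cost item.
- *Surgery start time:* not shown. Outside the covariate list it appears only in the Background, as a problem at the originating hospital: late operations left less time to recover before the day unit closed at 1800 hours. No text says that the programme reschedules operations, and no key recommendation in Table 1 concerns scheduling.
- *Informal care:* not shown. The Exclusion criteria section uses it to decide who is booked for a night in hospital, so it reads as a patient characteristic. Table 1 only has the breast nurse tell patients that it is needed.

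**2. What adjustment removes.** Let P be period (0 before, 1 after), M home care use (0/1) and Y the outcome, with Y = a + d·P + b·M + error. Let Δ be the programme-induced change in the proportion using home care.

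- Total pre-post effect (M left out): d + b·Δ
- Period coefficient with M in the model: d
- Part left out: b·Δ, which is zero if Δ = 0

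**3. Illustration.** The article gives neither b nor Δ, so all inputs are assumed: d = -1.0, b = +1.0, 20% use before. Simulated by least squares with 200,000 patients per period.

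| Rise in use (Δ) | Total by formula | Simulated, M left out | Simulated, M adjusted |
|---|---|---|---|
| 0 | -1.00 | -1.002 | -1.004 |
| 0.20 | -0.80 | -0.797 | -0.996 |
| 0.40 | -0.60 | -0.602 | -1.001 |
| 0.60 | -0.40 | -0.402 | -1.002 |

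Here adjustment *overstates* the effect.

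**4. Opposite direction.** With d = -1.5, b = -1.0 and Δ = 0.6 (also assumed), the total is -1.5 + (-1.0 × 0.6) = -2.10 and the adjusted estimate is -1.50. Here adjustment *understates* the effect, by 0.6/2.10 = 29%.

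**5. Costs.** Let c be the home-care cost per user. The programme adds Δ·c to the mean cost per patient: 0.2c for a 20-point rise and 0.6c for a 60-point rise. A cost model that holds home care use constant leaves this amount out of the increment.

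**6. Start time by the same method.** Assume an effect of 0.5 per SD of start time. With no programme-induced shift, adjusted and unadjusted effects agree (-1.00 and -1.00). With a shift of 0.5 SD, the total is -1.0 + 0.5 × 0.5 = -0.75 against an adjusted -1.00. Adjusting for start time is therefore a problem only if the programme moves it.

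**7. Precision.** If use rose from 20% to 80% with equal groups, the correlation of period with home care would be 0.60. The variance inflation factor would be 1/(1 - 0.36) = 1.56, and the standard error about 25% larger for a given residual variance. The range is 9% (30% to 70%) to 67% (10% to 90%). These rates are again assumed.

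**The case against.** The strongest reply is that the damage cannot be shown. The article gives neither home care use nor its effect on any outcome. If use does not change, nothing is lost, and every figure above rests on chosen inputs. That is right about size, but it does not defend the covariate. A programme that sets out to arrange home care can hardly be analysed on the premise that it leaves home care unchanged.

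A reader might also infer more than the article supports:

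- *That surgery start time and informal care are equally wrong.* The article does not say that the programme changes either. If it does not, both are legitimate covariates.
- *That the primary result is affected.* The primary outcome is the percentage treated in ultra short stay, and this model is described for interval-scaled outcomes only.
- *That the cost-effectiveness results are certainly biased.* The Programme cost-effectiveness section describes a before-after comparison and names no regression. Policy cost-effectiveness uses a separate model to combine the components. Costs are interval scaled, so a literal reading of the Statistical analyses section covers them, but the point remains conditional.
- *That baseline EuroQol and pre-surgery costs must be added.* A condensed article may leave baseline adjustment to the full plan. Pre-surgery costs are not clearly free of programme influence either, since Table 1 aims to keep preoperative visits to a minimum.

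**Conclusion.** The point holds for home care nursing and for the interval-scaled secondary outcomes. The plan as written estimates the period effect with home care held fixed, and so omits b·Δ from the programme effect. The direction depends on the sign of b, and the size cannot be computed from the article. Under the assumed inputs, the omitted part ranges from nothing (no change in use) to 0.6 of the home-care coefficient (a 60-point rise). The algebra assumes a linear model without interaction between period and home care.

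For costs the conclusion is conditional on this regression being used for them. If it is, the added home-care cost of Δ·c per patient leaves the increment and the programme looks cheaper by that amount.

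**What to change.** In the Statistical analyses section, make the main pre-post estimate for interval-scaled outcomes one without home care nursing as a covariate. Report the model that includes it only as an explanatory analysis of how the programme works. State whether this regression also governs costs and QALYs, and in any case do not adjust incremental costs for home care use. Surgery start time and informal care may stay unless the programme changes them, and one sentence should say whether it does.

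This is a change of wording before analysis. Dropping the covariate needs no new data and no change to the sample size or the primary analysis.

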### Economic evaluation

In the economic evaluation, programme cost-effectiveness will be combined with cost-effectiveness of the implementation strategy, to determine policy cost-effectiveness.

### Programme cost-effectiveness

The time horizon of six weeks seems appropriate as patients may receive additional treatment after surgery (e.g. radiotherapy, chemotherapy or hormone replacement therapy). Therefore, we expect that only short-term quality-of-life effects and costs can be attributed to the ultra short stay programme. Cost analysis includes health care costs and costs outside health care such as out-of-pocket costs or productivity costs due to reduction in paid work and/or domestic activities. Health care costs refer to hospital and other health care facilities costs. Hospital costs consist of personnel, material, capacity costs, and overhead, associated with the diagnosis, surgical treatment, hospital stay and follow-up. Other healthcare costs include costs of visits to the general practitioner, medication, home care etc. Health care costs are estimated by multiplying the resource utilization with the cost price per unit. Most of these costs are estimated by using existing resource registration systems and available cost prices through the financial departments of the participating centres. If true cost prices are not available in the participating centres, 1) existing cost prices of the uhM or 2) official directive prices are used[28]. Healthcare costs incurred outside the hospital and costs outside health care are partly estimated through a structured cost book that is kept by all participating breast cancer patients during the period of six weeks following discharge. Productivity losses due to absence from work are estimated through the friction cost method[28,29]. To perform the cost-effectiveness analysis, costs and effects of patients treated according to care as usual (before implementation) will be compared to costs and effects of patients treated according to the ultra short stay programme (after implementation).

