#### Exclusion criteria

Concerning surgical techniques, there is no contra-indication for ultra-short stay. Patients whose physiology impedes participation, as assessed by the breast surgeon and breast nurse, are excluded from the study. Patients who cannot rely on sufficient informal care in the home situation during the first night following surgery and patients with complaints that necessitate postoperative monitoring (e.g. cardial, pulmonal or neurological diseases) are scheduled for at least one overnight stay. This decision is made in consultation with the anaesthesiologist. The breast nurse scores the reasons for patients who do not participate.

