### Informed consent

Eligible patients are informed about the study by the breast nurse during a consultation separate from the consultation in which they are informed about the diagnosis breast cancer. Patients are given an informed consent form by the breast nurse when they are informed about the study, and they are asked to return the signed informed consent within a week. The informed consent regards consent to being asked to complete questionnaires with the aim to evaluate the cost-effectiveness of (the implementation of) the innovative care programme.

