### Cost-effectiveness of implementation

In each centre, the costs of the implementation process are calculated based on time and materials invested during the different phases of implementation. The diagnostic analysis may be looked upon as intervention. Its costs should be included in the costs of implementation. To determine cost-effectiveness of implementation, the costs of implementation will be weighed against the proportion of patients that is treated according to the ultra short stay programme.

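### Intention to treat is promised, but the cost-effectiveness comparison is worded as an as-treated one; the analysis set should be fixed as all pre-period versus all post-period participants

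*Protocol article*

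**What the plan says.** Statistical analyses section: "Intention to treat will be used for data analyses". The set is not defined further, and a pre-post design has no allocation from which to infer it.

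Programme cost-effectiveness section: the pre-period side is "costs and effects of patients treated according to care as usual (before implementation"; these are to be "compared to costs and effects of patients treated according to the ultra short stay programme (after implementation". The same section describes "a structured cost book that is kept by all participating breast cancer patients".

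Cost-effectiveness of implementation section: implementation costs are weighed against "the proportion of patients that is treated according to the ultra short stay programme". The Policy cost-effectiveness section then works with an extra cost per patient so treated and combines it with the programme result. Table 2 lists, as a process indicator, the reasons why patients did not receive ultra short stay as the protocol foresees.

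On the primary outcome, the abstract says: "Primary outcome measure is the percentage of patients treated in ultra short stay". Consecutive patients are eligible, but under Exclusion criteria: "Patients whose physiology impedes participation, as assessed by the breast surgeon and breast nurse, are excluded from the study". On consent: "The informed consent regards consent to being asked to complete questionnaires".

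**The concern.** The phrase that defines the post-period group in the cost-effectiveness comparison is used one section later for a proportion. The plan also expects some post-period patients not to be treated that way, since it records why. If those patients are left out after implementation while their counterparts stay in before it, the two groups differ in more than the care programme. Patients with co-morbidity, without informal care or with a difficult recovery would count in the pre-period mean and could be missing from the post-period one.

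At stake is the incremental cost per QALY, and with it the policy result built on top. The complication, emergency-visit and readmission counts that the article lists as part of programme effectiveness would be affected in the same way. Lower costs and better EQ-5D could then appear without any change caused by the programme.

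A smaller concern is that the physiology exclusion has no objective criterion and is judged by staff who know the period. One of the two assessors, the breast nurse, also coordinates the programme. If exclusions differ between periods, the denominator of the primary percentage shifts.

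**Working it through.** The article gives no figure for the size of this effect, so there is none to reproduce. The planned 40 patients per hospital per period does not bear on it.

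**1. The two readings side by side**

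| Wording | Points to |
|---|---|
| Post-period group described by how patients were treated | As-treated subset |
| Same phrase used as a proportion and as a per-patient unit in the two implementation sections | As-treated subset |
| Table 2 records reasons for not receiving ultra short stay | Such patients exist after implementation |
| Before/after labels in brackets | All patients by period |
| Cost book kept by all participants | All patients by period |
| Intention to treat | All patients by period |

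The literal wording supports the first reading and the context supports the second. The article does not choose.

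**2. Bias on the literal reading when the programme has no effect**

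Let *s* be the share of post-period patients in the subset. Let *d* be the amount by which those patients would cost less than the others in any case, on a scale where the overall mean is 100 in both periods. If the subset mean is *m*, then s·m + (1 − s)(m + d) = 100, so m = 100 − d(1 − s). The subset minus all pre-period patients is therefore −d(1 − s). All post minus all pre is 0.

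Inputs:
- *s* = 0.43, an assumption: the 13% baseline reported for the Maastricht hospital plus the 30-point target (Sample size calculations).
- *s* = 0.84, the later figure from the same hospital.
- *d* = 10, 20 or 30, assumed; the article gives no cost gap.

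| Uptake | d = 10 | d = 20 | d = 30 |
|---|---|---|---|
| 43% | 0.57 × 10 = 5.7 | 11.4 | 17.1 |
| 84% | 0.16 × 10 = 1.6 | 3.2 | 4.8 |

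Each entry is a spurious saving per 100.

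The same formula applies to QALYs. With an assumed EQ-5D gap of 0.05 held for the six-week horizon, the spurious gain is 0.57 × 0.05 × 42/365 = 0.0033 at 43% uptake and 0.16 × 0.05 × 42/365 = 0.0009 at 84%. The most that six weeks can yield is 42/365 = 0.115.

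At 43%, only about 0.43 × 40 = 17 post-period patients per hospital would remain in the comparison.

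**3. Counting uptake twice in the policy result**

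Suppose the programme changes outcome by *E* only in the additional short-stay patients, and the share rises by 0.30. All post minus all pre is then 0.30·E per participant, so uptake is already included. Multiplying by the change in share again would give 0.30 × 0.30·E = 0.09·E. The policy step must therefore match whichever set is used.

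**4. The exclusion and the primary percentage**

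Take a true change from 13% to 43% and assume that all excluded patients would not have been short stay. The observed share is the true share divided by (1 − excluded fraction).

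| Excluded pre / post | Observed change |
|---|---|
| 0% / 0% | 43 − 13 = 30 points |
| 20% / 20% | 53.75 − 16.25 = 37.5 |
| 0% / 20% | 53.75 − 13 = 40.75 |
| 20% / 0% | 43 − 16.25 = 26.75 |

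With no true change (13% in both periods), equal exclusion gives 0. Exclusion of 0%/20% gives 16.25 − 13 = +3.25, and 20%/0% gives −3.25.

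**The case against.** The strongest reply is that the as-treated set is only one reading. The period labels, the cost book kept by all participants and the stated intention to treat fit an all-pre versus all-post comparison. This stands: a reader might infer that the plan has settled on the subset, and the article does not support that.

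Second, the drop-out mechanism is not certain. Table 1 makes a planned night for patients with co-morbidity or insufficient supervision a key recommendation, and the programme covers stays of up to 24 hours. Such patients may count as treated under the programme. The abstract also lists short-stay percentage and treatment according to protocol as separate endpoints. So 43% is an illustration, and it does not follow that 57% of post-period patients would leave the comparison. This also stands.

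Third, the regression for interval-scaled outcomes adjusts for informal care, type of surgery and age. This helps in part; co-morbidity is not among the covariates.

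Fourth, a condensed article may leave analysis sets to the full protocol. That would excuse silence. Here two statements in the article pull apart, which is a different matter.

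On the primary outcome, a reader might infer that the exclusion breaches intention to treat or tilts the result towards the programme. Neither is supported. Exclusion before entry does not breach intention to treat, one rule is stated for both periods, and equal exclusion cannot create a change from none. Unequal exclusion can bias in either direction. Patients without informal care or needing monitoring are scheduled overnight and are not said to leave the study. Consent concerns questionnaires, and nothing says that non-consenters leave the primary denominator.

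**Conclusion.** The point holds as an inconsistency in the cost-effectiveness analysis set. If the wording is followed literally, selection enters the cost and QALY differences, and it favours the programme wherever the treated patients would have cost less or felt better anyway. In the illustration the spurious saving is about 6 to 17 per 100 at 43% uptake and 2 to 5 per 100 at 84%. These figures rest on an assumed gap of 10 to 30 per 100, on no programme effect, on no covariate adjustment, and on equating uptake with the short-stay share. If all participants by period are meant, this selection bias does not arise, but the policy step must then avoid applying uptake twice.

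Cost-effectiveness is a secondary endpoint, but it carries two of the six stated objectives, so the set should be fixed in advance.

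The exclusion is a lesser reporting point. It is subjective and could differ between periods, but neither the direction nor the existence of a bias in the primary percentage is shown.

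**What to change.** - In the Programme cost-effectiveness section, state that the main analysis compares all participating patients operated on in the pre period with all those operated on in the post period, whatever their actual stay.
- Make the as-treated comparison secondary, and define there what counts as treated under the programme.
- In the Policy cost-effectiveness section, state how the programme and implementation results are combined so that the change in short-stay share is applied only once.
- Report exclusions and their reasons by period. As a sensitivity analysis, give the primary percentage over all consecutive operated patients in each period, by actual admission type.

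The first three changes cost wording only. The last needs the admission type of excluded patients, whose reasons for not participating the breast nurse already records. The downside is a diluted cost-effectiveness contrast, since post-period patients who stayed longer are kept in; the secondary analysis shows the undiluted one.
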